#### Primary outcome

The primary outcome is the post-treatment assessment with the HRSD [23], which is the most widely used interview-based measure in depression studies [31]. The interview assesses depression severity. Outcome HRSD interviews are conducted by trained researchers who are blind to the research hypothesis, blind to the status of the patient (pre- or post-therapy), and thus also blind to treatment group. These researchers also conduct the post-treatment SCID-I interview.

#### Secondary outcomes

Self-report depression severity is measured by means of the Beck Depression Inventory (BDI-II [32]), which consists of 21 items and shows excellent reliability and validity. The presence of a diagnosis of depression (percentage of patients in remission) and other Axis I disorders is assessed post-treatment by means of the SCID-I interview [26] conducted by the researchers who also conduct the post-treatment HRSD interviews and thus are blind to treatment group and treatment status.

Global symptom severity and functioning are repeatedly measured by means of the Symptom Checklist-90 (SCL-90-R [33]), the shortened Depression Anxiety and Stress Scale (DASS [34]), and the Outcome Questionnaire-45 (OQ-45 [35]). Problems in interpersonal functioning are assessed by means of the Inventory of Interpersonal Problems-32 (IIP-32 [36]).

In line with recent recommendations [37], one to five idiosyncratic complaints are mapped during baseline assessment and rated by the participant at each session on a visual analogue scale (VAS) of 0–10.

#### Other measures

In addition to the prototype matching, commonly used measures for personality styles are included in the study. These are the Personal Style Inventory (PSI [38]) and the Depressive Experiences Questionnaire (DEQ [39]). Because of validity issues [9, 40], these are not used to categorize patients in one of the personality styles, but their administration allows further studies on convergence of different approaches to assess personality and compare results with other studies.

A number of additional measures are administered to provide more context to the other (self-report, interviews, and biological) measures, namely the Self-rating Inventory for Post Traumatic Stress Disorder (ZIL [41]), measuring trauma-related symptoms; the revised version of the Experiences in Close Relationships questionnaire (ECR [42]) designed to assess individual differences with respect to attachment-related anxiety and attachment-related avoidance; and the Short Temperament and Character Inventory (VTCI [43]), providing a comprehensive assessment of personality. These are administered a limited number of times (see Table 1). At every session, all participants rate ten emotions on a VAS of 0–10 [44].

To map the therapeutic relationship, which is considered a crucial variable in explaining outcome [45, 46], both therapists and patients fill out the Working Alliance Inventory-Short Revised (WAI-SR [47, 48]) every fourth session. Therapists additionally fill out the Therapist Response Questionnaire (TRQ [49]), and at each session a shortened version representing the seven main dimensions of the TRQ on a VAS of 0–10.

Finally, the semi-structured Client Change Interview (CCI) is administered around the 8th treatment session, at post-treatment, and at 6 and 24 months follow-up [50]. It inquires about experienced change, to what patients ascribe those changes, and the experience of therapy.

#### Biological measures

Biological measures comprise saliva, hair, and blood samples collected at different time points throughout the study (see Table 1). They will be used to assess cortisol levels as an indicator of stress and to explore biomarkers for depression in a broader way.

Saliva samples are a standard and well-validated way to measure hormonal fluctuations. They are administered before the first intake interview, before the first therapy session, before every fourth session, post-treatment, and at follow-up. Each time samples are administered early morning and late evening for 4 consecutive days [51]. Saliva samples are stored at –80° until analysis.

Hair samples are a more innovative method assumed to capture long-term systemic cortisol and consequently long-term stress, rather than momentary cortisol levels [52]. This relatively new method is thus less well validated than standard methods such as saliva samples. Samples are collected before treatment, around the 8th session, and post-treatment. A lock of about 4 mm diameter and 1–3 cm length is collected non-invasively by cutting it at the base of the vertex posterior of the head. Hair samples are stored in a dark and dry place until analysis. Cortisol concentrations in 1 cm of hair provide an indication of average cortisol level over the course of 1 month.

Blood samples are collected pre- and post-treatment. An independent lab administers them before 10 a.m. from a sober participant. Six tubes are collected: two 8-ml serum tubes, one 2-ml fluoride tube, one 2-ml EDTA tube, and one 9-ml EDTA tube. Screening of control variables is conducted within 12 hours after administration using a serum subsample, the 2-ml fluoride tube, and the 2-ml EDTA tube. The 9-ml EDTA tube is processed within 48 hours to extract DNA material, which will be stored at −80° for possible later (epi-)genetic analyses. Three other serum subsamples are stored at −80° for later analyses of biomarkers.

Mass spectometry techniques will be used for analyses of the different biological measures. For saliva samples, biomarker levels are averaged across the eight samples (4 days) to reduce daily variations.

#### Health care costs

The cost-effectiveness of therapy is assessed by means of health care cost information retrieved via the Inter-mutualistic Agency (http://www.nic-ima.be), covering a period starting 3 years pre-treatment until 2 years post-treatment (which is one of the only ways to gather objective information for a longer period before the patient entered the therapy; furthermore, it can be used to get an objective picture of antidepressant medication use). As these data are only useful when considered across a longer period and they can only be retrieved in the second wave of the study, they cannot be discussed in the primary results of the trial, but will be discussed in the second wave study on long-term outcome.

### Randomization and concealment

A (stratified) blocked randomization procedure with permuted blocks and allocation concealment to distribute dependent and self-critical patients evenly across the two types of treatment is used. An independent statistician from the Free University in Amsterdam (The Netherlands) generated the allocation sequence using the R package “Block Tools” [53]. Six trained research assistants who are blind to the allocation sequence conduct intake assessment. Only after the decision concerning eligibility is reached, will another researcher, unaware of any information on the patient, be contacted. This researcher handles the assignment to a treatment condition using the pre-generated allocation sequence. The peri- and post-interviews and follow-up assessments are conducted by the same research assistant who conducted the intake assessment, to minimize drop-out of the study. An independent researcher who is blind to the interventions and the study hypotheses conducts the primary outcome assessment (HRSD, SCID-I) immediately after treatment termination and before the post-interview (extended CCI) by the research assistant.

### Determination of sample size

Based on the literature, it can be expected that a wrong match between personality style and treatment approach can produce adverse treatment effects [4, 7, 10, 12, 13]. Therefore, we expect a large interaction effect between intervention type and personality size on the primary outcome of size 1.1 (Cohen’s *d*). To detect such an effect at the 5% significance level with at least 80% power, about 26 participants are needed in every intervention group in both strata (i.e., about 104 participants in total).

### Data analysis

Continuous variables will be summarized with means and standard deviations, median and interquartile ranges, and categorical variables with frequency tables.

The post-treatment score on the HRSD is the primary outcome. The primary hypothesis on the interaction between intervention type and personality style will be tested using a mixed model for the post-treatment score on the HRSD with baseline HRSD score (covariate), type of therapy, personality style, and the interaction of type of therapy and personality style as fixed effects and a random effect for every therapist. The latter is included to account for potential correlation in outcomes of patients assigned to the same therapist. Following the intention-to-treat approach, all randomized patients will be included in the analysis. The proposed mixed model approach is valid under the missing at random (MAR) assumption.

Secondary outcomes based on interviews (SCID and CCI) will be analyzed similarly to the primary outcome. Secondary outcomes based on self-reports (BDI, SCL, OQ, DASS, and idiosyncratic complaints), which are obtained at multiple sessions, will be analyzed using a mixed effects model approach with fixed effects of type of therapy, personality style, and its interaction at every time point; and a random effect for every therapist. The three-way interaction between therapy type, personality style, and time will be assessed to corroborate the primary hypothesis. The estimated evolution over time in each therapy group for each stratum will be graphically displayed. Effect sizes, reliable change indices (RCIs), and clinically significant change will be reported when possible for primary and secondary outcomes.

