### Outcomes and study measures

#### Procedure

There are measurement points at intake, before the start of therapy, at every session (limited self-report battery), at every fourth session (extended self-report battery), post-treatment, and at follow-up at 3 and 6 months. In the second wave of the study, additional follow-up is planned at 12 and 24 months, which can be extended if research means are available and if participants consent to prolonged follow-up. All interviews and therapy sessions are recorded on audiotape. Therapists write semi-structured reports of every session including an appreciation of their ability to work along the principles of the respective manuals, a description of the content of the session, and self-report scales. An overview of the full procedure and the respective measures that are used is presented in Table 1 according to SPIRIT guidelines [21, 22].

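### The primary model drops every randomized patient without a post-treatment HRSD, so it does not include all randomized patients, and its MAR validity holds only given the model's own covariates

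*Protocol article*

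**What the plan says.** All of this is in the protocol article.

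- **Response.** Data analysis: "The post-treatment score on the HRSD is the primary outcome".
- **Model.** Data analysis specifies "a mixed model for the post-treatment score on the HRSD with baseline HRSD score (covariate), type of therapy, personality style" and the therapy-by-style interaction "as fixed effects and a random effect for every therapist".
- **Population and missing data.** The same paragraph, invoking intention to treat, adds: "all randomized patients will be included in the analysis. The proposed mixed model approach is valid under the missing at random (MAR) assumption".
- **HRSD schedule.** Table 1 marks the HRSD twice, at enrollment and post-treatment. Recruitment and baseline assessment and Primary outcome agree. Randomization and concealment says that an independent researcher "conducts the primary outcome assessment (HRSD, SCID-I) immediately after treatment termination".
- **In-treatment data.** Procedure lists self-reports "at every session (limited self-report battery), at every fourth session (extended self-report battery"). In Table 1 the DASS belongs to the first set, and the BDI-II, SCL-90, OQ-45 and IIP-32 to the second. Data analysis places the BDI, SCL, OQ and DASS in longitudinal models as secondary outcomes.

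**The concern.** A mixed model keeps patients with incomplete follow-up when it has several responses per patient, because the observed ones carry information about the missing ones. This model has only one. The therapist effect links patients to each other, not a patient to his or her own other scores. So the inclusion sentence does not describe the model beside it.

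The MAR sentence is broader than the model supports. MAR given all observed data allows missingness to depend on scores recorded during therapy, and this model does not contain them.

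The gap matters in this trial because of its own hypothesis. Background reports that mismatch may hinder progress, and Determination of sample size bases the effect size on harm from a wrong match. Poor courses are therefore expected in two of the four therapy-by-style cells. If poor course leads to a missing HRSD, the contrast at risk is the interaction, which is the primary hypothesis. The report could still call the result intention-to-treat and valid under MAR.

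**Working it through.** **1. The plan's own sample size.** Inputs from Determination of sample size: interaction d = 1.1, 5% level (two-sided assumed), 80% power, four equal cells. A difference of differences has variance 4·SD²/n, with n per cell:

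n = 4 × (1.960 + 0.842)² / 1.1² = 4 × 7.85 / 1.21 = 25.9, rounded up to 26 per cell, or 104 in total.

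This reproduces the stated figure. Power at 26 per cell is Φ(1.1/√(4/26) − 1.960) = Φ(2.805 − 1.960) = 0.80 (0.793 by noncentral t on 100 df). The 104 therefore assumes an observed post-treatment HRSD for everyone.

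**2. Who enters the fit.** For patient i of therapist j the model is

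Y_ij = β0 + β1·baseline + β2·therapy + β3·style + β4·therapy×style + u_j + e_ij.

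The likelihood is built from the observed Y_ij. If Y_ij is missing, no other response of that patient is in the model, and his or her factor integrates to 1. The number analysed equals the number with a post-treatment HRSD.

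**3. Cost in numbers and power.** The missing fractions are assumptions. Power is Φ(1.1/√(4/n) − 1.960), with n = 26 × (1 − fraction).

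| Assumed missing | n per cell | Analysed of 104 | Power |
|---|---|---|---|
| 0% | 26 | 104 | 0.80 |
| 10% | 23.4 | 94 | 0.76 |
| 20% | 20.8 | 83 | 0.71 |
| 30% | 18.2 | 73 | 0.65 |

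**4. When the fit is valid.** With only the outcome missing, a fit to the observed outcomes is valid if missingness depends only on the model's covariates and therapist. This was checked by simulation: 4,000 replicates, 26 per cell, true interaction 1.10, unit-variance post score given baseline, therapist variance 0.05. For simplicity the fit was least squares without the therapist effect. A mid-treatment score outside the model shared a patient component with the post score. Missingness was logistic. All parameters are illustrative. The Monte Carlo standard error is about 0.007.

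| Missingness depends on | Mean number analysed | Mean estimate |
|---|---|---|
| nothing missing | 104 | 1.10 |
| baseline only | 79 | 1.10 |
| baseline, therapy, style and interaction | 75 | 1.11 |
| mid-treatment score, same in all cells | 83 | 1.07 |
| mid-treatment score, in mismatched cells only | 82 | 0.86 |

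The second and third rows show no material bias. The last two are diluted by (1.10 − 1.07)/1.10 = 3% and (1.10 − 0.86)/1.10 = 22%.

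A further simulation (2,500 runs, 20–24% missing, mid-treatment score correlated 0.5–0.8 with the post score) gave 0.94–1.07 for the model as written. It gave 1.09–1.12 after regression imputation from that single score. This supports using in-treatment information in principle; it does not test a full imputation procedure.

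**The case against.** Several stronger readings are tempting, and the documents do not support them.

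- **A reader might infer that a complete-case fit contradicts the MAR claim.** It does not. The second and third simulated rows show the fit performing as claimed when missingness depends on the model's covariates. The MAR sentence is too broad because it does not name the conditioning set; it is not false.
- **A reader might infer that the session-level scores are never used.** They feed the secondary longitudinal models, including a three-way interaction with time meant to support the primary hypothesis. They are absent only from the primary model.
- **A reader might equate leaving therapy with a missing HRSD.** The assessment is tied to the end of treatment, not to completing 16–20 sessions, and the protocol takes a step to limit loss from the study. An early leaver may still be assessed. Loss through poor course is plausible but not documented.
- **A reader might take 0.86 as the expected bias.** It needs an assumed mechanism that differs between matched and mismatched cells. Under other assumptions the bias is small or absent.

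The strongest general defence is that this is a condensed article and that imputation details belong in an analysis plan not shown. That is fair for the details. It does not rescue the inclusion sentence, which credits the stated model with a property it lacks. Invoking MAR at all concedes that some scores may be missing.

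**Conclusion.** The point holds in a limited form. The statement that all randomized patients are included is not true of the stated model unless no post-treatment HRSD is missing. That conclusion rests on the model and schedule alone and needs no simulation. The MAR statement holds conditionally on baseline HRSD, therapy, style and therapist. It fails to cover missingness that depends on the course during treatment, which the trial's own theory makes plausible.

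The practical size is uncertain because the documents give no dropout rate or mechanism. The power loss in step 3 depends only on the assumed missing fraction. The bias, from none to about 22% dilution of the interaction, depends on the assumed mechanism as well. Because the matter concerns the population and validity of the primary test, it should be settled before the analysis.

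**What to change.** 1. **Wording.** Say that the model as written uses patients with an observed post-treatment HRSD, analysed as randomized, and that its MAR validity is conditional on baseline HRSD, therapy, style and therapist.
2. **Primary estimate.** Fit the same ANCOVA mixed model after multiple imputation of missing post-treatment HRSD. Use one imputation model with therapy, style, their interaction, baseline HRSD and a small set of auxiliaries, for example the last available and the post-treatment BDI-II. Add auxiliary-by-cell terms only as the data allow. A joint longitudinal model of HRSD and BDI-II is an equivalent option. All randomized patients then enter the primary analysis.
3. **Keep it parsimonious.** Imputing separately within each cell from every self-report score is not workable. At 20% missing there would be about 26 × 0.8 = 20.8 observed outcomes per cell, against more than 30 predictors if every DASS, BDI-II and OQ-45 score were used. Sessions 17–20 may also legitimately not occur.
4. **Sensitivity.** Add a delta-adjusted analysis and report the complete-case fit as supportive.

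The cost is wording and modest programming, since the auxiliary data are already collected. The downside is reliance on an imputation model, which the sensitivity analyses help the reader to judge.

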**Fig. 1 Fig1:**
[figure not shown]
SPIRIT flow diagram of progress through the phases of the Ghent Psychotherapy Study

**Table 1 Tab1:** SPIRIT schedule of enrollment, interventions, and assessments

	Study period									
	Enrollment	Allocation	Post-allocation					Close-out 1		Close-out 2
Time point	-t1	0	t1	t2	t3	t4	t5	t6	t7	t8
Enrollment										
Eligibility screening	x									
Informed consent	x	x								
Allocation		x								
Interventions										
CBT			x	x	x					
STPP			x	x	x					
Assessment										
- Interviews:										
HRSD	x					x				
SCID I	x					x				
SCID II	x									
CDI	x									
CCI					x	x	x	x	x	x
- Self-report scales:										
BDI-II, SCL-90, OQ-45, IIP-32	x			x	x	x	x	x	x	x
DASS, VAS	x		x	x	x	x	x	x	x	x
Idiosyncratic scale			x	x	x	x	x	x	x	x
WAV				x	x					
DEQ, PSI	x					x		x		x
VTCI, ECR	x					x				
ZIL	x				x	x				
- Biological measures										
Saliva samples	x		x	x	x	x	x	x	x	x
Blood samples	x					x				
Hair samples	x				x	x				
- Therapist measures										
Structured report, VAS			x	x	x					
TRQ, VAS				x	x					

t1: sessions 2–3, 5–7, 9–11, 13–15, 17–19; t2: sessions 1, 12, 16, 20; t3: session 8; t4: post; t5: 3 month follow-up; t6: 6 month follow-up; t7: 12 month follow-up; t8: 24 month follow-up

*HRSD* Hamilton Rating Scale for Depression, *SCID I* Structured Clinical Interview for DSM-IV-TR Axis I Disorders, *SCID II* Structured Clinical Interview for DSM-IV-TR Axis II Disorders, *CDI* Clinical Diagnostic Interview, *CCI* Client Change Interview, *BDI-II* Beck Depression Inventory II, *SCL-90* Symptom Checklist -90, *OQ-45* Outcome Questionnaire-45, *IIP-32* Inventory of Interpersonal Problems-32, *DASS* Depression Anxiety Stress Scales, *VAS* Visual analogue scale, *WAV* Working Alliance Inventory, *DEQ* Depressive Experiences Questionnaire, *PSI* Personal Style Inventory, *VTCI* Short Temperament and Character Inventory, *ECR* Experiences in Close Relationships, *ZIL* Self-rating Inventory for Post Traumatic Stress Disorder, *TRQ* Therapist Relationship Questionnaire

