The baseline assessment takes place at the Faculty of Psychology and Educational Sciences of Ghent University and is conducted by a team of postgraduate research assistants trained in the respective procedures. Before the first intake interview, patients receive a baseline battery of questionnaires and provide eight saliva samples (a morning and evening sample for 4 consecutive days) to measure baseline symptom presence and severity, personality characteristics, and stress levels before the first face-to-face contact with the researcher. During the face-to-face assessment, the Clinical Diagnostic Interview (CDI, [25]), the HRSD [23], and the Structured Clinical Interview for DSM-IV Axis I disorders [26] and Axis II disorders [27] are administered in two respective interview appointments with the same researcher. The CDI is a semi-structured interview that assesses both the current clinical complaints and a range of current and lifetime inter- and intrapersonal experiences. This interview is used to rate the dependent and self-critical personality organization by means of prototype matching [24]. The rating takes place after the CDI and before the HRSD and SCID to limit any possible bias by the formal diagnosis. Three independent and trained researchers (interviewer, one postgraduate researcher, and one academic staff researcher) conduct the prototype matching. They each score the interview individually and consequently discuss their scores. To be possibly included in the trial, a score of at least 3 on a scale of 1 to 5 for one of the personality dimensions and a minimum of 2 points difference with the score on the other personality dimension are required. When no agreement can be reached, the difference in consensus scores between dependent and self-critical personality dimensions is less than 2 points, or there is no score of at least 3 on either dimension, patients are excluded from the trial. The HRSD and SCID-I depression module are used to assess severity of depressive symptoms and the diagnosis of MDD, respectively. The SCID-I and II are also used to assess co-morbidity and exclusion criteria. The baseline procedure finally yields the collection of a hair sample and a blood sample. Together with the saliva samples, these form the baseline for the biological component of the study.

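### The models for the repeated self-report outcomes leave out the intake score, so the therapy by style contrasts at each time point are unbiased but less precise than the collected data allow

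*Protocol article*

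**What the plan says.** The Data analysis section specifies two kinds of model and lists the fixed effects of each.

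- **Primary outcome.** The post-treatment HRSD is analysed in a mixed model "with baseline HRSD score (covariate), type of therapy, personality style, and the interaction of type of therapy and personality style as fixed effects", with a random effect for therapist.
- **Repeated self-reports.** "Secondary outcomes based on self-reports (BDI, SCL, OQ, DASS, and idiosyncratic complaints), which are obtained at multiple sessions" are given a separate mixed model. Its fixed effects are therapy, style and their interaction, each specific to the time point, and its only random effect is for therapist. No baseline score is listed. The section then assigns the three-way interaction of therapy, style and time the task of supporting the primary hypothesis.

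The intake scores exist. Under Recruitment and baseline assessment, before the first interview "patients receive a baseline battery of questionnaires". Table 1 marks the row "BDI-II, SCL-90, OQ-45, IIP-32" and the DASS row in the enrollment column, ahead of allocation. The idiosyncratic scale has no mark there, so this point does not extend to it. IIP-32 shares the marked row but is not in the self-report list of the Data analysis section, so it is left aside here.

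The Data analysis section does not say whether intake counts as one of the modelled time points.

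**The concern.** A contrast between four cells of 26 patients is imprecise, and the self-reports are meant to support the HRSD result. Randomization is stratified by personality style, and no severity factor is named, so intake scores on these scales are balanced between therapies only by chance. The primary contrast will be adjusted for its own baseline; the self-report contrasts set beside it will not be. The two could then differ partly because one uses the baseline and the other does not. The data needed to avoid this are already collected.

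**Working it through.** **Inputs.** From Determination of sample size: an interaction of 1.1 ("we expect a large interaction effect between intervention type and personality size on the primary outcome of size 1.1"), the 5% level and power ("To detect such an effect at the 5% significance level with at least 80% power"), and the size ("about 104 participants in total", that is 26 in each of four cells). Two-sided testing is assumed, since sidedness is not stated. The correlation r between the intake score and a later score on the same scale is not in the article; 0.3, 0.5 and 0.7 are assumptions. Equal variances at intake and later are also assumed.

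**1. Reproduce the plan's figure.** Read as a difference of differences in SD units, the contrast has variance 4/n for n per cell. So n = 4 × (1.960 + 0.842)² / 1.1² = 25.95, rounded up to 26 per cell and 104 in total. Power at 26 is 80.1%. The figure reproduces with no allowance for baseline adjustment.

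**2. One time point, unadjusted.** SE = √(4/26) = 0.392 SD. The difference detectable with 80% power is 2.802 × 0.392 = 1.099 SD.

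**3. The same contrast with the intake score as covariate.** SE = 0.392 × √(1 − r²).

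| r (assumed) | 1 − r² | SE (SD) | Detectable at 80% power (SD) | Unadjusted total with equal precision, 104/(1 − r²) |
|---|---|---|---|---|
| none used | 1.00 | 0.392 | 1.099 | 104 |
| 0.3 | 0.91 | 0.374 | 1.048 | 114 |
| 0.5 | 0.75 | 0.340 | 0.952 | 139 |
| 0.7 | 0.51 | 0.280 | 0.785 | 204 |

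A simulation of 40,000 trials with 26 per cell gave empirical SDs of 0.39 unadjusted and 0.375, 0.341 and 0.280 adjusted, in agreement with the formula.

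**4. Where chance imbalance sits.** The intake imbalance on the interaction contrast itself has an SD of 0.392. It enters the unadjusted later contrast with weight r, so a one-SD imbalance moves the estimate by 0.12, 0.20 or 0.27 SD at r = 0.3, 0.5 or 0.7. This is not additional to step 2. At r = 0.5 the unadjusted variance is 4/26 = 0.1538. Of that, 0.25 × 0.1538 = 0.0385 comes from imbalance and 0.1154 is the rest, and √0.1154 = 0.340, the adjusted SE. Adjustment removes exactly the imbalance part.

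**5. The three-way test, under both readings of the time points.**

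- *Intake is a time point with its own free effects.* With complete data the post-treatment contrast is still the raw difference of cell means. The three-way test becomes in part a comparison of change from intake. For a contrast of two time points, a change score has relative variance 2(1 − r), against 1 − r² under covariate adjustment: 1.40 v 0.91, 1.00 v 0.75 and 0.60 v 0.51 at r = 0.3, 0.5 and 0.7. It also over-corrects. In simulation the change estimate correlated −0.59, −0.50 and −0.38 with intake imbalance, against about 0 after covariate adjustment.
- *Intake is not a time point.* A stable effect of intake severity largely cancels when later times are compared with each other, so the three-way test changes little.

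**The case against.** The strongest reply is that an article gives one sentence to several models and leaves the rest to an analysis plan. That covers the coding of time and the covariance structure. It covers the baseline term less well, because the article lists the fixed effects of both models and names a baseline covariate in only one.

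A second reply stands in part. The article's supporting test is the three-way interaction, and the figures in the table describe a therapy by style contrast at one time point. They are not the precision of a repeated-measures test over many sessions, and the change-score comparison covers two time points only. The power calculation was made for the HRSD; no power is claimed for the self-reports.

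Four stronger readings are tempting, and the article does not support them:

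- A reader might infer that the self-report estimates are biased. Under randomization they are not, in expectation.
- A reader might count chance imbalance as a second harm beside lost precision. Step 4 of the working shows that it is the same cost.
- A reader might infer that imbalance passes into the three-way test in proportion to r. That holds for the contrasts at each time point. The three-way test either over-corrects or is little affected.
- A reader might think it enough to keep intake as a response and give both therapies a common intake mean. With only a therapist random effect, that constraint does not adjust the later contrasts, because nothing links a patient's intake score to the same patient's later scores.

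**Conclusion.** The point holds for the therapy by style contrasts at each time point on BDI-II, SCL-90, OQ-45 and DASS. These contrasts are valid but inefficient as specified. Adjusting for intake would lower their variance by 9%, 25% or 49%, and their standard error by about 5%, 13% or 29%, at r = 0.3, 0.5 or 0.7. At the low end of that range the gain is small. The size rests on r, which the article does not give, on 26 evaluable patients per cell, and on equal variances over time.

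For the three-way test the effect depends on whether intake is a modelled time point, which the article leaves open. Only secondary outcomes are concerned. The change is worth making because it needs no new data and the self-reports are meant to bear on the primary hypothesis.

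**What to change.** In the Data analysis section, or in the analysis plan, state for BDI-II, SCL-90, OQ-45 and DASS:

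- *The intake score of the same scale and its interaction with time enter as covariates, and only assessments after allocation are modelled as outcomes.*
- *The adjusted therapy by style effect at post-treatment is the supporting contrast and is reported alongside the three-way interaction.*

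An alternative is to keep intake as a response with a common mean for the two therapies within each personality style. This must come with a within-patient covariance, for example unstructured or through a patient random effect; without it the constraint does not adjust later time points.

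The cost is a few extra model parameters. Under the covariate option, intake also appears in the plots of evolution over time as an observed value only and not as a modelled one.
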